### Questionnaires

Study patients will complete a validated German version of the Cognitive Failures Questionnaire for self-assessment (s-CFQ) [29]. Close relatives of the patients will answer a cognitive questionnaire to evaluate foreign assessment (f-CFQ) [30]. The questionnaires will examine the frequency of failures in daily living related to memory, attention, action, and perception. Because memory impairment is an important element that affects everyday functioning, the s-CFQ was modified with additional questions related to memory failures, taken from the validated German version of the Memory Complaint Questionnaire [31]. Depression and anxiety will be scored using the validated German version of the Hospital Anxiety and Depression Scale (HADS) [32]. HQL will be assessed using the Short Form-36 (SF36) questionnaire [33]. The SF36 covers eight health-related factors including vitality, physical functioning, bodily pain, general health perceptions, physical role functioning, emotional role functioning, social role functioning, and mental health. The HADS will be used at every neuropsychological test time point; the s-CFQ, f-CFQ and SF36 will be completed at baseline and 3 and 12 months after discharge from rehabilitation.

### Magnetic resonance imaging

Cranial MRI will be performed 6–10 days after surgery using a 3-T scanner (Skyra; Siemens, Erlangen, Germany). The protocol of imaging will include a T2-weighted turbo spin-echo sequence (slice thickness = 3 mm, field of view (FOV) = 220 × 220 mm, matrix = 512 × 391, repetition time (TR) = 7490 ms, echo time (TE) = 100 ms), a T2-weighted turbo spin-echo sequence for dark fluid (slice thickness = 3 mm, FOV = 220 × 220 mm, matrix = 320 × 224, TR = 7000 ms, TE = 81 ms), a T1-weighted FLASH sequence (slice thickness = 3 mm, FOV = 220 × 220 mm, matrix = 320 × 320, TR = 250 ms, TE = 2.49 ms) and a diffusion-weighted echo-planar imaging sequence (slice thickness = 3 mm, FOV = 220 × 220 mm, matrix = 160 × 160, TR = 7720 ms, TE = 64 ms, slice gradients of *b* values = 0 and 1000 s/mm^2^). The postoperative diffusion-weighted sequence will be used by two blinded, experienced observers for registration and planimetric evaluation of acute ischemic lesions.

### Primary outcome measure

The primary outcome measure will be the training effect on all objectively measured neuropsychological functions at discharge from rehabilitation.

### Secondary outcome measure

As a secondary outcome, we will evaluate the training effect of all objectively measured neuropsychological functions at 3 and 12 months after discharge from rehabilitation. Second, we will evaluate the training effect on the subjective self-assessment and external assessment by relatives of cognitive failures at 3 and 12 months after discharge from rehabilitation. Third, we will evaluate the training effect on HRQ at 3 and 12 months after discharge from rehabilitation. Fourth, we want to investigate the extent to which the cognitive training has an impact on depression at all follow-up time points. Last, we will examine the impact of perioperative cerebral ischemia on the neuropsychological measured training effect at all follow-up time points. Perioperative cerebral ischemia will be measured with postoperative DW-MRI during the first postoperative week. The number and size of ischemic lesions are determined and will be used as a control variable for the analysis of the training effect.

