### Planned statistical analyses

The effect of cognitive training will be analyzed by repeated measures (mixed between-within) analysis of variance (ANOVA) with groups (control group/intervention group) as the between-subject factor and assessment time (baseline and all follow-up assessments) as the within-subject factor for all cognitive tests and questionnaires, respectively. Assumptions for repeated measures ANOVA will be tested using the Levene test for variance-homogeneity and Mauchly’s test for sphericity. If sphericity is violated, alpha levels will be adjusted using the Greenhouse-Geisser correction. Normal distribution will be tested using the Shapiro-Wilk test. To control for the possibility of confounder variables that could affect the results, we will conduct additional repeated measures analysis of covariance (ANCOVA), which includes covariates such as preoperative cognitive values, age, sex, education, psychiatric scores (depression/anxiety), and perioperative variables such as duration of extracorporeal circulation, administration of anesthesia, and number and size of ischemic lesions.

Post hoc explorative between-subject comparisons will be analyzed using the *t* test for independent samples. In this case, we will compare the intervention group with the control group by calculating a change score in cognitive values (post-training score minus pre-training score). The change in cognitive values is the dependent variable, and the treatment group (cognitive training group/control group) is the independent variable.

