## Discussion

The aim of this study is to evaluate a paper-and-pencil-based cognitive training program for patients undergoing heart surgery with extracorporeal circulation. POCD shows the highest incidence of neurological complications that can occur in the context of surgery, especially cardiac surgery [1]. Adverse effects of POCD on daily living abilities can be noticed by patients themselves and their relatives in both the short and long term [6]. The etiology remains controversial but can be considered a multifactorial event in which extracorporeal circulation plays a crucial role [8].

Here, we present cognitive training that integrates well with standard rehabilitation, takes place as early as possible, and aims to reduce the occurrence and persistence of cognitive deficits in the short and long term. It is also of interest whether patients with perioperative ischemic stroke benefit from this intervention to varying degrees or in different forms.

We intentionally opted for technically simple paper-and-pencil-based training tasks because POCD after cardiosurgical procedures mainly affects elderly people. Many studies on the effect of cognitive training have used computer-based training tasks [15], which provide the advantage of generating and capturing data simply, quickly and very precisely. However, even today, they often represent an unfamiliar medium for older people, which could lead to irritation, fear of contact, and/or frustration in the older population studied here and thus constitute a potential bias. A placebo intervention for the control group is intentionally omitted because cognitive effects of placebo interventions on cognitive performance are difficult to control. In order to credibly suggest to patients that the placebo intervention could have an influence on their memory and thus also to achieve a willingness to participate, the structure of the placebo intervention will have to be closely related to cognitive training (e.g., relaxation exercises, crossword puzzles, conversation therapy, computer games, etc.) and thus also achieve cognitive training effects.

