The only prospective investigation of patients undergoing cardiac surgery to date reported a beneficial effect of memory and attentional training in patients who underwent CABG [19], but no information was given on the use of extracorporeal circulation in this collective. In this study, training took place between the 6th and the 10th week following surgery. However, it is still not clear when the optimal time point for cognitive training should be set and for how long the intervention should be carried out. It seems possible that the rehabilitation of postoperatively impaired cognitive function will be more improved by an earlier intervention starting in the range of a week compared to one month after surgery. Controlled studies on neurorehabilitation of post-stroke cognitive impairment have shown beneficial effects for several cognitive functions when restitutive cognitive training begins within 2 weeks [40] or about 7 months [17] after stroke onset. Animal models suggest a time-dependent increase in neuroplasticity (plastic window) after ischemic injury, with a peak at 7–14 days and near completion at 30 days. Nevertheless, it should be noted that the assignability of these findings from bench to bedside is difficult, and the shape and extent of the neuroplastic window in humans remains unclear [41].

In our study, the detection of acute, perioperative cerebral ischemia is performed by MRI with DWI. With the use of DWI, a preoperative baseline assessment is not necessary because in this sequence, acute ischemic tissue is presented as a bright area that typically occurs 2–3 h after the onset of damage and usually subsides within 2–3 weeks [42]. These acute cerebral ischemic lesions can be detected by DW-MRI in 14–61% of the patients after cardiac surgery [11, 43]. The significance of those acute MRI lesions, especially with regard to manifestation of POCD, remains unclear [42]. To our knowledge, there are no studies controlling for the potentially confounding effect of peri-interventionally endured cerebral ischemia detected during the first postoperative week. In this context, it seems of particular interest whether patients with acute cerebral ischemia benefit from cognitive training to any other degree or in any other form.

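### Lesion number and size enter only as control variables, so the secondary question of whether ischemia changes the training effect gets no estimate

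*Protocol article*

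**What the plan says.** The Secondary outcome measure section gives as its last outcome: "we will examine the impact of perioperative cerebral ischemia on the neuropsychological measured training effect at all follow-up time points". The Abstract and the Background list the same item. The Discussion says what is meant, in two places: "It is also of interest whether patients with perioperative ischemic stroke benefit from this intervention to varying degrees or in different forms", and again "whether patients with acute cerebral ischemia benefit from cognitive training to any other degree or in any other form".

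For the analysis, the Secondary outcome measure section states: "The number and size of ischemic lesions are determined and will be used as a control variable for the analysis of the training effect". The Planned statistical analyses section describes a repeated measures ANOVA "with groups (control group/intervention group) as the between-subject factor and assessment time (baseline and all follow-up assessments) as the within-subject factor". An additional repeated measures ANCOVA, introduced as a check on confounders, has "number and size of ischemic lesions" among its covariates. The article names no term combining group and lesion, no lesion subgroup and no estimate stratified by lesion status.

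**The concern.** Whether ischemia alters the benefit of training is a question of effect modification: does the difference between arms vary with lesion burden? Entering lesions as a covariate answers another question, namely what the training effect is once differences in lesion burden have been allowed for. That model takes the training effect to be the same at every lesion burden.

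The Background presents the trial as the first to explore the impact of ischemia on cognitive training after cardiac surgery. As written, that secondary outcome would have no estimate. A training effect that hardly moves after adjustment could then be read as showing that ischemia does not matter for benefit, which an adjusted main effect cannot show. If an interaction were added only after the data were seen, the lesion measure and the time point would be open to selection.

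**Working it through.** **1. Aim against method**

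- Aim: impact of ischemia on the training effect, explained as benefit to a different degree (Secondary outcome measure; Discussion).
- Model factors: group and time (Planned statistical analyses).
- Lesions: control variable or covariate (Secondary outcome measure; Planned statistical analyses).

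In the repeated measures setting the training effect is group × time, so its modification by lesions is group × lesion × time. Some software adds lesion × time when a covariate is entered. That term describes how lesions relate to cognitive change with both arms pooled, so it still does not measure a difference in benefit.

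**2. The plan's own figures**

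The Power and sample size estimation section uses η² = 0.10, 80% power and two-sided 5%.

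- f = √(0.10/0.90) = 0.333, so d = 2f = 0.667.
- The noncentral F distribution gives power 0.797 at 36 and 0.808 at 37 per group, which reproduces 37.
- Three intervals with 20% dropout: 37/0.8³ = 72.3, in line with the 72 stated.

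These figures concern the main training effect. None is given for the ischemia question.

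**3. What the covariate model returns**

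Suppose, for illustration, a training effect of 0.667 SD without lesions and 0 with lesions. The covariate-only model then averages the two:

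- 14% prevalence: 0.86 × 0.667 = 0.57 SD
- 61% prevalence: 0.39 × 0.667 = 0.26 SD

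A simulation (2,000 runs, 115 patients) gave the same two values. A model with the group × lesion term rejected equal benefit in 23% and 41% of runs, and in about 5% when the effects really were equal. It targets the right quantity, with low power.

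**4. Precision of the interaction at discharge**

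Inputs: 72 × 0.8 = 57.6 per group; prevalence p from 14% to 61% (Discussion). Assumptions: lesion yes/no, balanced across arms, MRI available for all, outcome SD of 1, no gain from baseline adjustment.

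SE = √[2/(57.6p) + 2/(57.6(1−p))]; interaction detectable with 80% power ≈ 2.8 × SE.

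| p | SE (SD units) | 2.8 × SE |
|---|---|---|
| 0.14 | 0.537 | 1.50 |
| 0.30 | 0.407 | 1.14 |
| 0.50 | 0.373 | 1.04 |
| 0.61 | 0.382 | 1.07 |

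The article gives no correlation between baseline and follow-up scores. If it is r, baseline adjustment multiplies the SE by √(1−r²):

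- r = 0.5: factor 0.87, detectable interaction about 0.9–1.3 SD
- r = 0.7: factor 0.71, detectable interaction about 0.7–1.1 SD

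Without that gain, an interaction as large as the planned main effect (0.667 SD) has power of about 0.24 at 14% prevalence and 0.41 at 61%. At 12 months, with 74 patients in total, the detectable interaction is 1.88 SD at 14% and 1.34 SD at 61%.

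**The case against.** The strongest reply is that adjustment may be what was intended. The Discussion notes that earlier studies did not control for a potentially confounding effect of ischemia. The Study design and enrollment section speaks of acute pathology that could confound both the testing and the training effect. On that reading the covariate fits its purpose, and the differential-benefit wording is only an expression of interest. This justifies keeping the adjustment. It does not remove the other question: the impact on the training effect is listed as an outcome in its own right, and the Discussion twice explains it as differing benefit.

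A second reply is that an interaction term is a detail for a full protocol or analysis plan not shown here, the covariate list being open-ended. Pure silence could be excused in that way. Here, however, the article states how the lesion data will be used for the training effect, and that use does not match the aim.

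A third is that the interaction is underpowered. That is correct, and it limits how the result may be reported. It argues for an exploratory estimate with a wide interval rather than for a model that gives none.

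Some stronger readings go beyond the text:

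- A reader might infer that the MRI is done mainly for this question. The Study design and enrollment section also gives screening for hemorrhage and other acute pathology as its purpose.
- A reader might take the planned correlations as the lesion analysis, and fault them for relating lesions to scores. They are described generically and do not mention lesions.

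**Conclusion.** The point holds as a mismatch between a stated secondary outcome and the only stated analysis of the lesion data: no planned model estimates whether ischemia modifies the training effect. This follows from the form of the model and does not depend on the power figures.

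The size of the remaining uncertainty does depend on assumptions. With a yes/no lesion variable balanced across arms, 57.6 per group at discharge, 14–61% prevalence and no baseline gain, the interaction SE is about 0.37–0.54 SD. Power of 80% is then reached only at about 1.0–1.5 SD, or about 0.7–1.1 SD with an assumed baseline correlation of 0.7. A reader might conclude that smaller interactions would be missed; the figures show only that power for them falls below 80%. A continuous lesion measure would have a different precision.

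Nor do the documents support the inference that the sample size is wrong or the primary result compromised. The 37 and 72 per group reproduce, and the primary conclusion at discharge is unaffected.

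**What to change.** For this secondary outcome, add a group-by-lesion-by-time term to the planned repeated measures ANCOVA. A group-by-lesion term in a baseline-adjusted model at each follow-up would serve the same end. The article describes no separate discharge ANCOVA, so the choice should be written down.

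- Name one lesion measure in advance: presence/absence, or number or volume. A yes/no measure is simple to report but discards the number and size information being collected.
- Report the training effect with a 95% CI by lesion status (or at stated lesion burdens), together with the interaction estimate and its CI.
- Label the analysis exploratory, and keep it under the planned FDR control.
- Keep lesion number and size as adjustment covariates, and say that this adjustment addresses confounding and not differential benefit.

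No new data or patients are needed. The cost is a modest amount of extra modelling and tabulation across the cognitive tests and three follow-up times, and intervals that will be wide.

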### Cognitive training

There is currently only one study in which effective cognitive training was performed in patients undergoing cardiac surgery [19]. This study used a combination of computer-based training (with a focus on selective attention) and memory strategy training (method of loci). We decided against this training concept because we think that our elderly patients are not familiar with the use of computers, and we will therefore use a purely paper-and-pencil approach. Second, memory strategies seem to be less effective than cognitive exercises such as computerized or paper-and-pencil procedures [34]. To our knowledge, there is no specific cognitive domain that clearly emerges over time in the context of POCD, such as memory or attention. Therefore, we decided to train several cognitive functions that are used especially in everyday life to maintain social functions and earning capacity. These include word fluency, working memory, attention, and the ability to plan.

For the preparation of our training program we first conducted a literature search on German-language-validated paper-and-pencil-based cognitive exercise methods. The literature is very scarce. In a controlled study design, a training program by Müller et al. (2004) [35] showed cognitive improvements in patients with executive dysfunction [36]. Their program included training in word fluency, cognitive flexibility, working memory, and planning ability. However, we found the cognitive training of Müller et al. (2004) [35] in some parts to be too unentertaining for our patients, whereby we took over only a few training tasks and combined them with new tasks designed by our group to achieve better acceptance.

Cognitive training in the intervention group will include paper-and-pencil-based exercises practicing multi-domain cognitive executive functions such as word fluency, verbal and visual working memory, selective visual attention, and planning. One training session will last approximately 40 min and will be performed 6 days a week for 3 weeks.

The daily training program consists of eight different types of standardized tasks addressing the processing of words, categories, images, head calculation, and planning. New words, categories, images, head calculations, and planning tasks will be presented on each training day. Each task takes between 2 and 10 min; to manage the working time, the patients must limit their work using a digital clock. At the beginning of the training program, a trained investigator will give explicit instructions in a one-to-one training session and will be nearby to help with any questions about the exercises. If no further help is needed in the following training days, the patient will be provided with training material for the following 6 days so that patients can complete the training independently in their ward rooms. Each task contains precise written instructions that can be used to assist in its execution. If a patient has questions about the training, he or she can contact the trainer. After every 6th day, the extent to which the tasks have been completed is checked by the training investigator and new training material will be provided. Patients are told that their exercise solutions are not evaluated or corrected. Therefore, it does not matter whether the solutions are right or wrong. An important concern for the patients is that they concentrate on the tasks and cognitively exert themselves. In this way, we can avoid possible performance pressure and also avoid patients exchanging the right approaches among themselves. The different types of tasks are presented in the following standardized order.

#### Phonetic word fluency

The patient is given three letters on a sheet of paper. Within 2 min, he or she has to note as many words as possible that begin with these letters. This task is mainly intended to train word fluency and was adapted from Müller et al. (2004) [35].

#### Categorical word fluency

In this task, the patient is given three different categorical terms on a sheet of paper. Within 2 min, as many words as possible that can be assigned to these categories must be found and noted. This task is mainly intended to train word fluency and was adapted from Müller et al. (2004) [35].

#### Comic strips

Patients receive 4–5 popular German comics from German illustrators such as Wilhelm Busch, Erich Ochser or Hans Jürgen Press, with 3–16 pictures of a story in mixed order. Within 5 min, the pictures have to be arranged mentally in a meaningful order. The new invented order should be documented by numbering the pictures with a pencil. This task is mainly intended to train working memory and was created by our group.

#### Mental arithmetic

The patient is asked to complete several calculation tasks on a sheet of paper. The result of the first arithmetic problem, which includes addition, subtraction and multiplication of numbers, must be memorized. In the second step, another calculation task must be solved, and the result must also be memorized. In the last step, the last result should be subtracted from the first result, and the final result should be written down. The time limit for this exercise is 5 min. This task is mainly intended to train working memory and was adapted from Müller et al. (2004) [35].

#### Synonymic fluency

The next worksheet contains three different terms. For each term, patients must find words with similar meanings (synonyms). For example, if the term is *wallet*, then other words would be *portmonee* or *money purse*. The time limit is 2 min. This task is mainly intended to train word fluency and was created by our group.

#### Fill in the blank text

In the next training task, short stories are presented. These are generally known stories by Wilhelm Busch, the Brothers Grimm, Hans Christian Andersen or fables from antiquity, German studies, Buddhism, and Japan. The stories have gaps that have to be filled in with a self-chosen, meaningful word. The time limit for this exercise is 5 min. This task is mainly intended to train word fluency and working memory and was constructed by our group.

